## Section 4: Protocol Synopsis

### 4.1 Study Design

#### 4.1.a. Detailed description

Rural counties, particularly in Appalachia, are battling fast-growing outbreaks of HIV. One of the most promising mechanisms for reducing HIV transmission in these communities is the use of buprenorphine which treats opioid use disorder and also decreases HIV risk. Despite the potential benefit of buprenorphine, health care professionals (HCPs) in rural areas of the United States are much less likely to have received the training and federal waiver necessary to prescribe this medication. The single biggest obstacle to extensive MOUD use is stigma—stigma among communities, families of people who use drugs (PWUD), and remarkably, among HCPs.

We recently completed a study demonstrating that OUD-related stigma is common among physicians in Ohio. This stigma is greater among physicians practicing in rural areas—the same areas experiencing the greatest impact of the opioid crisis. Stigma is also associated with fewer buprenorphine prescribers, syringe service programs, and naloxone dispensaries in the surrounding county. Physicians' stigma toward PWUD is predicted by 3 key attitudes that are unique to the opioid crisis and which require tailoring of existing training interventions.

Rural health care professionals would benefit from brief stigma-reduction training interventions but to date effective stigma-reduction interventions have not been tailored specifically for MOUD or for the rural primary care setting. Adapting MOUD-specific interventions that are feasible and acceptable for health care professionals practicing in rural areas is critical for improving access to buprenorphine in underserved rural communities.

This study includes developmental activities aimed at isolating the modifiable features of OUD-related stigma among rural health care professionals, adapting a brief stigma-reduction training intervention and finalizing the intervention with health care professional feedback, and implementing a two-arm randomized pilot trial among rural health care professionals to assess feasibility and acceptability of the intervention. We hypothesize that the brief stigma-reduction training intervention will be both feasible and acceptable in the rural primary care setting. Our specific aims are to:

Aim 1: Examine HCP knowledge and attitudes about OUD to understand their reluctance to prescribe MOUD and manage patients with OUD.

Aim 2: Develop a narrative-based stigma reduction intervention and tailor it to the rural primary care setting using HCP feedback.

Aim 3: Assess the feasibility and acceptability of a stigma-reduction intervention in a pilot study in a diverse group of rural primary care HCPs.

To adapt existing interventions, we will disseminate a focused survey to 300 rural primary care physicians in Ohio, assessing key features of stigma and the relationship to buprenorphine attitudes and use. Prior to screening, we will also pre-test all survey items with 25 health care professionals with similar characteristics to our target population. The pilot will assess survey length, and check response distribution, item comprehension, and data collection procedures.

To assess intervention components, we will provide the intervention to 15 rural health care professionals and conduct a structured focus group to explore each module, assess perceptions of the intervention, identify the most salient features, and isolate barriers of concern to inform the development of a booster module.

To understand perceptions of each component in greater depth, we will conduct in-depth interviews with 15 rural health care professionals who have received the intervention.

Following completion of the booster module, we will provide the intervention to 15 rural additional health care professionals and conduct a structured focus group to assess perceptions of the booster module, identify needed changes to each module in the overall intervention, and finalize the intervention for feasibility testing.

Screening, enrollment, randomization and assessments. We will enroll 400 HCPs across 6 rural FQHCs who (1) currently practice in Ohio and (2) are eligible buprenorphine prescribers under federal law (3) do not currently prescribe buprenorphine at full capacity. Primary care providers will include physicians with board certification in internal or family medicine as well as family nurse practitioners. Because our primary outcomes are intervention feasibility, clinics will be cluster randomized into a group of 4 (intervention arm, n=267) and 2 (control arm, n=133) to increase the amount of pilot data on the intervention. We will recruit practices from Federally Qualified Health Centers (FQHCs) and FQHC look-alikes in rural, Ohio counties affiliated with OACHC. All eligible participants in enrolled practices will be screened for eligibility and asked to complete the study.

Enrolled participants will be evaluated at baseline, immediately following the intervention, and at 3 and 6 months after enrollment. The baseline and follow-up questionnaires will be administered via an online survey.

Follow-up in-depth interviews will be conducted to monitor the process of change in primary and secondary outcomes over time. Over the enrollment period, we will select 10 participants in the intervention arm. We will purposively select 4 individuals who newly prescribed buprenorphine during this period, 3 individuals who were not retained in the study, and 3 individuals who did not prescribe buprenorphine at all. Interviews will be conducted by key personnel who are trained interviewers. Each interview will last approximately 60 minutes.

#### 4.1.b. Primary purpose

Health Services Research

#### 4.1.c. Interventions

Name: Brief OUD Stigma-Reduction Training Intervention

Description: The Brief OUD Stigma-Reduction Training Intervention is comprised of several modules aimed at decreasing stigma, increasing knowledge about medications for OUD, and increasing willingness to prescribe buprenorphine among rural HCPs currently in practice. The first module provides an introduction to the aims of training and the study overview. Module 2 provides education about OUD in the rural context, current standards of care, and buprenorphine prescribing and regulation. Module 3 includes a narrative-based interview with a patient in recovery from OUD, focusing on the context of opioid initiation and the role that buprenorphine played in recovery. Module 3 also includes a second narrative-based interview with a primary care provider who was initially hesitant to work with this patient population and prescribe buprenorphine but currently does so and finds the work meaningful. The final module provides resources for additional training and a direct link to X waiver certification as well as a reminder about future data collection points. Participants will complete interactive quizzes after each module and continuing education or continuing medical education (CE or CME) credit will be provided after completion of the full training. An interactive, booster module will be provided after one month which focuses on anticipated problems and barriers faced by providers prescribing buprenorphine.

Study Phase: N/A

Interventional Study Model: Parallel

Masking: Yes, Investigator, Outcomes Assessor

Allocation: Randomized

## Outcome Measures:

| Type    | Name            | Time Frame | Brief Description                                                                                                                                                                                                                                                                                                                                                                                                                                                                                                                                                                                                                                                                      |
|---------|-----------------|------------|----------------------------------------------------------------------------------------------------------------------------------------------------------------------------------------------------------------------------------------------------------------------------------------------------------------------------------------------------------------------------------------------------------------------------------------------------------------------------------------------------------------------------------------------------------------------------------------------------------------------------------------------------------------------------------------|
| Primary | Acceptability   | 3 months   | 
Acceptability is the perception that the intervention is agreeable, palatable, or satisfactory to health care professional participants. Acceptability will be assessed qualitatively and quantitatively.
 
We will administer to participants the Acceptability of Intervention Measure (AIM), which comprises 4 items containing responses on a 5-point Likert scale. We will also record participants' perceptions and feedback about the intervention modules. In in-depth interviews, we will explore the stakeholders' perceptions of the content of the intervention, the need for it in rural practice settings, its potential effectiveness, and ease of delivery
 |
| Primary | Feasibility     | 3 months   | 
Feasibility refers to the ease in which a new intervention can be used within a specific setting. It will be measured using the 4-item FIM. We will also measure feasibility through interviews with health care professional participants to understand barriers and facilitators of implementing the intervention in the rural primary care setting.
                                                                                                                                                                                                                                                                                                                          |
|         | Appropriateness | 3 months   | 
Appropriateness refers to the perceived alignment of the intervention within a particular practice setting and will be measured by the 4-item Intervention Appropriateness Measure (IAM). We will also measure appropriateness in in-depth interviews with health care professionals, exploring the most salient features of the intervention and its fit with current training needs.
                                                                                                                                                                                                                                                                                          |
| Primary | Adoption        | 6 months   | 
Adoption refers to intentions or actions to adopt an EBI. We will measure adoption as whether a HCP initiates buprenorphine prescribing for the first time or increases their patient panel (yes/no) and as the total number of patients receiving buprenorphine for each HCP. This measure will also allow us to measure preliminary effect sizes related to buprenorphine prescribing which are critical for the
                                                                                                                                                                                                                                                              |

|           |                                            |          |                                                                                                                                                                   |
|-----------|--------------------------------------------|----------|-------------------------------------------------------------------------------------------------------------------------------------------------------------------|
|           |                                            |          | follow-up cluster randomized trial to test intervention effectiveness.                                                                                            |
| Secondary | Training and prescribing waivers           | 6 months | Whether the participant completed any additional training (yes/no) and whether the participant received an X-waiver (yes/no)                                      |
| Secondary | Prescribing knowledge                      | 6 months | Knowledge of buprenorphine standards of care                                                                                                                      |
| Secondary | Willingness to work with patients with OUD | 6 months | 5-item scale ( $\alpha=0.87$ ) assessing willingness to work with patients with OUD.                                                                              |
| Secondary | Attitudes toward patients with OUD         | 6 months | 10-item scale ( $\alpha=0.81$ ) assessing bias toward patients with OUD, adapted from a previously validated scale measuring bias toward people who inject drugs. |

Subject participation duration: 24 months

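### The adoption outcomes pool first-time initiation with any panel growth and the model has no baseline prescribing term, which dilutes the effect and exposes it to chance differences in prescriber mix

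*Combined protocol and SAP*

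**What the plan says.** **Who enrols.** Section 4.1.a requires HCPs to be "eligible buprenorphine prescribers under federal law (3) do not currently prescribe buprenorphine at full capacity". Only prescribers at full capacity are excluded, so never-prescribers and current prescribers with room on their panel both qualify.

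**Adoption (primary, 6 months).** The Outcome Measures table gives two forms. The binary form is "whether a HCP initiates buprenorphine prescribing for the first time or increases their patient panel (yes/no"). It sets no minimum increase and no reference panel. The second form is defined "as the total number of patients receiving buprenorphine for each HCP", with no mention of change from baseline. The table adds that adoption will supply preliminary effect sizes for the follow-up trial.

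**X-waiver (secondary, 6 months).** The outcome is "whether the participant received an X-waiver (yes/no"). It is not limited to HCPs who lack a waiver at baseline. Section 4.1.a describes rural HCPs as "much less likely to have received the training and federal waiver necessary to prescribe this medication".

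**Design and model.** In section 4.1.a, "clinics will be cluster randomized into a group of 4 (intervention arm, n=267) and 2 (control arm, n=133"), with no stratification or matching stated. On timing, "Enrolled participants will be evaluated at baseline, immediately following the intervention, and at 3 and 6 months after enrollment". The model under Analyses of primary outcomes has a random subject effect, a fixed clinic effect and outcomes at 3 and 6 months. It names no baseline prescribing or waiver term and no subgroup. The section on expected effect size and power refers to a difference-in-differences design, but the model does not carry this through.

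**The concern.** One yes/no is asked of two groups for whom it means different things. A non-prescriber scores yes only by starting to prescribe, which is the behaviour the training targets. A current prescriber scores yes if the panel is one patient larger, which ordinary turnover produces often.

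Three consequences follow:

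- The effect on initiation is diluted by a group with a high background rate.
- With four clinics against two, prescriber share can differ between arms by chance, and nothing in the model corrects for it. The patient total is hit hardest because it carries the baseline panel directly.
- The effect size passed to the follow-up trial depends on a case mix that the plan does not undertake to report.

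The waiver outcome has a related gap. If a waiver is needed to prescribe, current prescribers already hold one. They then either cannot succeed or succeed automatically, depending on what *received* means.

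**Working it through.** **Stated figures.** The documents give no baseline prescriber share, panel size, turnover, initiation rate or between-clinic variation, so there is no plan figure on this point to reproduce. The detectable difference of d = 1.01 cannot be rebuilt either, because no intraclass correlation is stated. It would need about 0.16 (normal approximation) or 0.08 (t with 4 df) at 4:2 clinics and N = 400. It is not shown to be wrong, and nothing below depends on it.

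**Step 1: chance panel growth.** Assume a stable Poisson panel with mean L in which a fraction t turns over. Joiners and leavers are each Poisson(tL), so

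P(increase) = [1 − exp(−2tL)·I0(2tL)] / 2,

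where I0 is the modified Bessel function of order zero. Setting t = 1 gives two independent counts.

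| L | t = 0.3 | independent counts |
|---|---|---|
| 3 | 0.336 | 0.417 |
| 5 | 0.378 | 0.436 |
| 10 | 0.417 | 0.455 |

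So about 34% to 45.5% of current prescribers would score yes with no real change. At 20% turnover and L = 3 the figure is 29%.

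**Step 2: imbalance with no intervention effect.** Let w be the share of current prescribers, g their chance-growth rate and p the initiation rate in non-prescribers. The pooled rate is w·g + (1 − w)·p, so the arm difference is (w_I − w_C)(g − p).

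- With p near 0, a 10-point imbalance gives 0.10 × 0.336 to 0.455 = 3.4 to 4.6 points. A 20-point imbalance gives 6.7 to 9.1 points.
- With p = 5% and g = 40%: shares of 30% vs 20% give 15.5% vs 12.0% (+3.5 points); 40% vs 20% give 19% vs 12% (+7); 20% vs 40% give −7.
- For the patient total, the shift is (w_I − w_C) × L. At 10 points this is 0.3, 0.5 or 1.0 patients per HCP for L = 3, 5 or 10. With an overall share near 20% the average is 0.2 × L, so the shift is half of it.

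**Step 3: how likely is such an imbalance?** If clinic shares have SD s, the arm difference has mean 0 and SD s × √(1/4 + 1/2). That is 0.087 for s = 0.10 and 0.130 for s = 0.15 (both assumed). More than 10 points then occurs in about 25% to 45% of allocations, and more than 20 points in about 2% to 12%. In simulation with no effect and 60 HCPs per clinic (400 × 0.90 / 6), a test ignoring clinics rejected in 12% to 19% of trials; a cluster-level t test rejected in about 5%.

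**Step 4: dilution with balanced arms.** Assume initiation of 5% vs 15%, and 40% chance growth in both arms with no effect on it. The pooled difference is (1 − w) × 10 points. Power uses the usual two-proportion formula (pooled variance under the null, unpooled under the alternative), unclustered, with 120 vs 240 retained HCPs. It serves only for relative comparison.

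| w | Pooled rates | Difference | Risk ratio | Power, pooled | Power, non-prescribers only |
|---|---|---|---|---|---|
| 0 | 5% vs 15% | 10 | 3.0 | 84% | 84% (120 vs 240) |
| 0.20 | 12% vs 20% | 8 | 1.67 | 47% | 73% (96 vs 192) |
| 0.40 | 19% vs 25% | 6 | 1.32 | 24% | 59% (72 vs 144) |

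The last column uses the smaller denominator.

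**Step 5: waiver.** Let h be the share already holding one. If only new waivers count, the maximum is 1 − h, and a 10-point effect among the unwaivered becomes 8 points at h = 0.20 and 6 at h = 0.40. If held waivers count, a 10-point imbalance in holders, with 10% newly waivered in both arms, creates 10 × (1 − 0.10) = 9 points with no effect.

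**Step 6: can a baseline covariate be added to the model as written?** Six clinic indicators plus arm make 7 columns of rank 6, because arm is the sum of its clinics' indicators. Arm is therefore not estimable beside fixed clinic effects, with or without the covariate.

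**The case against.** A reader might infer that the adoption contrast simply reflects baseline clinic mix. The documents do not support that. Clinics are randomized, so imbalance is as likely to favour one arm as the other and its expectation is zero. A valid cluster-level test keeps its error rate near 5%; the 12% to 19% arises only when clinics are ignored, which is a separate fault.

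A reader might also infer that waiver holders cannot succeed on the waiver outcome. That holds only if *received* means newly received, which the plan leaves open. On the other reading they succeed automatically.

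Further points for the plan have weight:

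- Panel growth looks like an intended target. The eligibility rule, "do not currently prescribe buprenorphine at full capacity", leaves room for it, and the booster module in section 4.1.c addresses barriers met by those already prescribing. Restricting primary adoption to non-prescribers would change the estimand.
- The binary item is already a within-HCP change, and patient numbers are already a separate measure.
- A 20-point imbalance is a tail case under the assumed spread, and a low prescriber share would make it less likely still.
- This is a pilot.

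These arguments remove the bias claim and any case for dropping the pooled outcome. They do not answer the dilution, the missing baseline term or the undefined waiver outcome. Deriving effect sizes is the pilot's stated use for adoption.

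**Conclusion.** The point holds as a matter of dilution, lost precision and exposure to chance imbalance, not of systematic bias. The pooling and the absence of a baseline prescribing term are plain in the documents. The sizes are not: prescriber share, panel size, turnover, initiation rate and between-clinic spread are all assumptions. Within them, a 10-point imbalance is an ordinary event and can move binary adoption by about 3 to 5 points.

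The more dependable harm needs no imbalance, since the risk ratio handed to the next trial varies with a case mix that may differ there. The dilution figures assume no effect on panel growth among current prescribers. If the training does raise it, dilution is smaller, but the two effects still cannot be told apart in the pooled result.

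**What to change.** 1. Keep the pooled outcome if it is wanted. Adjust the adoption model for baseline prescriber status, and the patient count for baseline panel.
2. State the reference panel (for example, the baseline count) and the minimum increase that counts as growth.
3. Report initiation among baseline non-prescribers and panel change among baseline prescribers separately, and use these as the effect sizes for the follow-up trial.
4. Define the waiver outcome as a new waiver among HCPs without one at baseline.
5. Fit clinic as a random effect or analyse at cluster level. Without this, step 1 does not yield an arm effect.
6. Tabulate baseline prescriber and waiver shares by clinic and arm.

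The cost is mainly SAP wording. A baseline survey is already planned, and the eligibility screen and the panel-increase definition already require prescribing status and panel size. Waiver status may need one added item. The downside is a smaller denominator for each separately reported component.

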## Power Analyses

### 4.3 STATISTICAL DESIGN AND POWER

#### **Number of subjects we expect to enroll for the quantitative assessments:**

400 provider participants

#### **Expected effect size and power:**

Given that this is a pilot study that will be used to power a future R01, we do not have sufficient data about the psychometric properties of the outcome measures utilized in this study among our population of interest, including the means and standard deviations. As such, we cannot estimate the specific degree of change we can detect in terms of scale points. Thus, the sample size estimation is based on a differences-in-differences cluster randomized trial with two parallel arms and a continuous outcome variable. Alpha was set to 0.05 and power was estimated at 80%. We estimate retention to be 90% at 6 months, due to limited job turnover within community health centers enrolled in the study. Based on these assumptions, a sample of 400 provides 80% power to detect a difference of  $d = 1.01$  with participants clustered in 6 clinics. This indicates we will have sufficient power to assess a difference of one standard deviation in each of the primary outcome variables.

